# The Effects of Propofol Cardioplegia on Blood and Myocardial Biomarkers of Stress and Injury in Patients With Isolated Coronary Artery Bypass Grafting or Aortic Valve Replacement Using Cardiopulmonary Bypass: Protocol for a Single-Center Randomized Controlled Trial

**DOI:** 10.2196/resprot.3353

**Published:** 2014-07-08

**Keywords:** cardiac surgery, anesthetics, cardiopulmonary bypass, ischemia, reperfusion, cardioplegia, aortic valve, coronary artery, troponin, clinical trials, randomized

## Abstract

**Background:**

Despite improved myocardial protection strategies, cardioplegic arrest and ischemia still result in reperfusion injury. We have previously published a study describing the effects of propofol (an anesthetic agent commonly used in cardiac surgery) on metabolic stress, cardiac function, and injury in a clinically relevant animal model. We concluded that cardioplegia supplementation with propofol at a concentration relevant to the human clinical setting resulted in improved hemodynamic function, reduced oxidative stress, and reduced reperfusion injury when compared to standard cardioplegia.

**Objective:**

The Propofol cardioplegia for Myocardial Protection Trial (ProMPT) aims to translate the successful animal intervention to the human clinical setting. We aim to test the hypothesis that supplementation of the cardioplegic solution with propofol will be cardioprotective for patients undergoing isolated coronary artery bypass graft or aortic valve replacement surgery with cardiopulmonary bypass.

**Methods:**

The trial is a single-center, placebo-controlled, randomized trial with blinding of participants, health care staff, and the research team. Patients aged between 18 and 80 years undergoing nonemergency isolated coronary artery bypass graft or aortic valve replacement surgery with cardiopulmonary bypass at the Bristol Heart Institute are being invited to participate. Participants are randomly assigned in a 1:1 ratio to either cardioplegia supplementation with propofol (intervention) or cardioplegia supplementation with intralipid (placebo) using a secure, concealed, Internet-based randomization system. Randomization is stratified by operation type and minimized by diabetes mellitus status. Biomarkers of cardiac injury and metabolism are being assessed to investigate any cardioprotection conferred. The primary outcome is myocardial injury, studied by measuring myocardial troponin T. The trial is designed to test hypotheses about the superiority of the intervention within each surgical stratum. The sample size of 96 participants has been chosen to achieve 80% power to detect standardized differences of 0.5 at a significance level of 5% (2-tailed) assuming equal numbers in each surgical stratum.

**Results:**

A total of 96 patients have been successfully recruited over a 2-year period. Results are to be published in late 2014.

**Conclusions:**

Designing a practicable method for delivering a potentially protective dose of propofol to the heart during cardiac surgery was challenging. If our approach confirms the potential of propofol to reduce damage during cardiac surgery, we plan to design a larger multicenter trial to detect differences in clinical outcomes.

**Trial Registration:**

International Standard Randomized Controlled Trial Number (ISRCTN): 84968882; http://www.controlled-trials.com/ISRCTN84968882/ProMPT (Archived by WebCite at http://www.webcitation.org/6Qi8A51BS).

## Introduction

During cardiac surgery with cardiopulmonary bypass (CPB), a cardioplegia (heart-stopping) solution is used to arrest the heart. Although beneficial for the surgical procedure, the oxygen/nutrient deficit and restriction in blood supply (ischemia) can result in myocardial damage and dysfunction. In addition, restoration of oxygenated blood flow (reperfusion) after a period of ischemia can cause further (and often more severe) damage. This is known as ischemia/reperfusion (I/R) injury.

Loss of control over cellular calcium mobilization and the generation of reactive oxygen species (ROS) are known to be key events critical to the induction of I/R damage [1]. Elevated intracellular calcium leads to the destruction of mitochondrial cell membrane integrity [2] and eventual recruitment of macrophages and neutrophils to the area causing further damage to surrounding tissue. There are several sources of ROS generation with all species interacting with numerous cellular targets. ROS attack a wide range of biological molecules resulting in deleterious wide-ranging effects, including attack of the cardiomyocyte [3]. Furthermore, cytosolic calcium loading and the generation of ROS can result in the opening of the mitochondrial permeability transition pore (MPTP). Mitochondrial disruption consequently leads to cardiomyocyte death [1,4].

Strategies to protect the heart during cardiac surgery include interventions that target the mitochondria, such as alteration of cardioplegia temperature, method of delivery and composition, and the use of calcium transport modulators and/or inhibitors of the MPTP [1,5-11]. A number of anesthetic agents have also been implicated in cardioprotection strategies [12-14]. Inhalation anesthetics have been shown to decrease myocardial oxygen demand and contractility [15] and intravenous anesthetics have been shown to exhibit antioxidant effects [16]. Both are reported to play a role in the reduction of the systemic anti-inflammatory response.

Propofol is a general anesthetic widely used for the induction and maintenance of anesthesia during cardiac surgery and for postoperative sedation. In addition to its anesthetic effect, propofol has been reported to confer protection against damage to the myocardium during oxidative stress [17] and reperfusion [18,19]. Various mechanisms have been proposed to explain this cardioprotective effect, including inhibition of plasma membrane calcium channels [20,21], free radical scavenging [22-25], and enhancing antioxidant capacity [26,27]. Furthermore, reports have shown propofol can inhibit the MPTP in isolated mitochondria [28,29], although nonclinical concentrations were employed in these studies.

We have previously published a study describing the effects of propofol on metabolic stress, cardiac function, and injury in a clinically relevant animal model of normothermic cardioplegic arrest and CPB [30]. We were able to conclude that cardioplegia supplementation with propofol at a concentration relevant to the human clinical setting resulted in improved hemodynamic function, reduced oxidative stress, and reduced I/R injury when compared to standard cardioplegia.

The aim of our current trial is to translate propofol supplementation from our animal model to a human clinical setting by investigating the benefits of using propofol as an adjunct to cardioplegia for patients undergoing coronary artery bypass grafting (CABG) or aortic valve replacement (AVR) surgery using CPB. Specific objectives are:

To estimate mean differences in biomarkers of cardiac injury and metabolism between groups of participants having isolated CABG with CPB using warm blood cardioplegia with propofol supplementation vs supplementation with placebo.To estimate mean differences in biomarkers of cardiac injury and metabolism between groups of participants having AVR with CPB using cold blood cardioplegia with propofol supplementation vs supplementation with placebo (intralipid).

## Methods

### Overview

The Propofol cardioplegia for Myocardial Protection Trial (ProMPT) is designed as a single-center, placebo-controlled, randomized trial. Participants, health care staff, and members of the research team involved in data collection or providing health care, except for the perfusionist, are blinded to a participant’s allocation.

### Trial Population and Recruitment Procedure

Patients undergoing nonemergency isolated CABG or AVR with CPB at the Bristol Heart Institute (BHI) are being invited to participate.

Participants may enter the trial if they are male or female, between 18 and 80 years, having elective or urgent CABG or AVR with CPB, and are able to give full informed consent for the trial. Patients may not enter the trial if any of the following apply: (1) previous cardiac surgery, (2) combined CABG and AVR, (3) emergency or salvage operation, (4) chronic renal failure requiring dialysis, (5) current congestive heart failure, (6) left ventricular (LV) ejection fraction <30% (ie, poor LV function), (7) allergy to peanuts, eggs, egg products, soybeans, or soy products (these are intralipid ingredients), or (8) participating in another interventional trial.

Potential trial participants are identified from operating theater lists and are sent or handed an invitation letter and information leaflet that has been approved by a NHS Research Ethics Committee (REC). They have at least 24 hours to consider whether to participate. If there is insufficient time to consider taking part, a potential participant is not approached to ask for written informed consent.

After admission to the BHI, patients are seen by a member of the research team who answers any questions, confirms eligibility, and requests and witnesses written informed consent. Details of all patients approached for the trial and reasons for nonparticipation (eg, reason for being ineligible or declining consent) are being documented.

### Randomization

Each participant is randomly assigned in a 1:1 ratio within CABG or AVR surgery stratum to standard cardioplegia with either propofol (intervention) or intralipid (placebo) supplementation using a secure, concealed, central Internet-based randomization system (Sealed Envelope Ltd). Standard cardioplegia is warm blood for CABG and cold blood for AVR. Randomization is minimized by diabetes mellitus status, defined as requirement for oral or insulin medication to control blood sugar at the time of admission. A member of the Clinical Trials and Evaluation Unit (CTEU) Bristol who is not involved in data collection or providing health care randomizes a participant shortly before surgery and communicates the allocation to the perfusionist. If a participant is unexpectedly rescheduled, the trial number and randomized allocation is retained.

### Intervention and Placebo

#### Overview

Propofol (Fresenius Propoven 1%) is licensed for the induction and maintenance of anesthesia and is used for these purposes by most cardiac anesthetists at the BHI.

Intralipid emulsion is used as the vehicle for propofol administration; therefore, they have exactly the same consistency and milky appearance. It has been suggested that intralipid is itself cardioprotective (based on recovery of cardiac function in rats) [31], but it does not appear to confer protection against cardiac injury [32]. We wish to test the specific hypothesis that propofol supplementation is cardioprotective and a recognized mechanism is postulated. For these reasons, intralipid has been chosen as the placebo for this trial.

Propofol is diluted in a 1:5 ratio with 0.9% sodium chloride as recommended by the manufacturer to achieve a working solution of 2000 μg/mL. Intralipid is diluted in the same manner.

Propofol and intralipid for use in the trial are labeled and dispensed by the Bristol Royal Infirmary (BRI) pharmacy in accordance with Good Clinical Practice (GCP).

#### Standard Cardioplegia Composition and Delivery

Calafiore warm blood cardioplegia (for CABG): A 60 mL syringe is prepared with 20 mL of 15% potassium chloride (2 mmol K^+^/mL) and 5 mL of 50% magnesium sulfate (2 mmol Mg^2+^/mL), resulting in a ratio of 4:1 potassium:magnesium in the syringe driver. A roller pump draws oxygenated blood from the oxygenator and the potassium–magnesium mixture is added by syringe pump downstream. Intermittent antegrade delivery is used according to local protocol.

Cold blood cardioplegia (for AVR): A 500 mL prebagged solution of Harefield Hospital Formulation (IVEX Pharmaceuticals Ltd, Larne, Northern Ireland, UK) is used. A roller pump draws up oxygenated blood from the oxygenator and the cardioplegia solution is added in a 4:1 blood:cardioplegia ratio. Cold cardioplegia is given at a temperature of approximately 4°C and by either antegrade or retrograde delivery (or a mixture of both) according to local protocol.

#### Anesthetic Management and Supplementation of Cardioplegia

Anesthetic management adheres strictly to a locally agreed protocol (see Multimedia Appendix 1) and all other aspects of the patient’s preoperative and postoperative management are in accordance with existing protocols in use in the BHI.

For CABG procedures, propofol (or intralipid) is added to the cardioplegia by attaching an additional syringe pump to the line, downstream of the blood oxygenator (Figure 1). For AVR procedures, propofol (or an equivalent volume intralipid) is added directly to a 500 mL bag of 4:1 cardioplegia solution (Figure 2).

For both intervention groups, the cardioplegia solution (blood–cardioplegia mix) has a final concentration target of 6 μg/mL of supplemented propofol. This concentration is significantly below the level routinely observed in the circulation during induction of anesthesia for cardiac surgery, but higher than during maintenance of anesthesia when cardioplegia is administered (ie, a concentration to which the myocardium is routinely exposed).

**Figure 1 figure1:**
[figure not shown]
CABG warm blood cardioplegia. Propofol is first diluted from 10,000 μg/mL to 2000 μg/mL using 0.9% sodium chloride. The diluted propofol solution is added to the cardioplegia by attaching an additional syringe pump to the line downstream of the blood oxygenator. This method is identical to that used for adding potassium and magnesium to the oxygenated blood. The syringe driver is set to 0.6 mL/min resulting in a 6 μg/mL supplementation of the blood/cardioplegia mix during delivery. For the placebo group, cardioplegia is supplemented with placebo in the same manner as described for propofol. In the event addition of propofol is indicated, this is substituted with an equivalent volume of intralipid.

**Figure 2 figure2:**
[figure not shown]
AVR cold blood cardioplegia. Propofol is first diluted from 10,000 μg/mL to 2000 μg/mL using 0.9% sodium chloride. Diluted propofol is added directly to a 500 mL bag of 4:1 cardioplegia solution by 1:1 (vol:vol) substitution. For the placebo group, cardioplegia is supplemented with placebo in exactly the same manner as described for propofol. In the event addition of propofol is indicated, this is substituted with an equivalent volume of intralipid.

### Primary Outcome

The primary outcome is myocardial injury, assessed by measuring myocardial troponin T in serum from blood samples collected preoperatively and at 1, 6, 12, 24, and 48 hours after chest closure (Figure 3). Although absolute times of sampling after reperfusion could vary between participants, blinding of the intervention prevents any systematic difference between groups.

**Figure 3 figure3:**
[figure not shown]
Measurement of myocardial injury and propofol concentration. The primary outcome is myocardial injury, assessed by measuring myocardial troponin T in serum from blood samples collected preoperatively and at 1, 6, 12, 24, and 48 hours after chest closure. The concentration of plasma propofol is measured in blood samples collected from the cardioplegia/bypass circuit immediately before aortic cross-clamping, once during cardioplegia (after blood–cardioplegia mixing), and 10 min post cross-clamp release.

### Secondary Outcomes

Data are collected to characterize the following secondary outcomes:

Myocardial ischemic stress assessed using biopsies taken from left and right ventricles immediately before aortic cross-clamping and 10 minutes after cross-clamp release. Gene expression and cellular changes associated with stress and injury-signaling pathways are to be studied in a small subset of biopsies using metabolite/RNA extracts.Systemic metabolic stress assessed by measuring lactate in blood samples collected preoperatively and 1, 6, 12, 24, and 48 hours after chest closure.Blood pH measured by using the blood samples collected preoperatively and 1, 6, 12, 24, and 48 hours after chest closure.Renal function assessed by measuring creatinine in serum from blood samples collected preoperatively and 1, 6, 12, 24, and 48 hours after chest closure.The concentration of plasma propofol measured in blood samples collected immediately before aortic cross-clamping, once during cardioplegia (after blood–cardioplegia mixing), and 10 minutes after cross-clamp release (Figure 3). Blood is taken from the cardioplegia/bypass circuit.Length of intensive care unit (ICU) / high-dependency unit (HDU) stay.Clinical outcomes and serious adverse events (SAEs), such as serious postoperative morbidity (eg, myocardial infarction, permanent stroke, renal failure defined as new need for hemodialysis) and death from any cause. Case report forms used for data collection specify 26 SAEs that are anticipated after cardiac surgery.Patient health status monitored using customized questionnaires administered preoperatively and completed by participants as a postal questionnaire 3 months postoperatively. Also, CABG and AVR patients are asked to complete the Coronary Revascularisation Outcome Questionnaire (CROQ) [33] and the Minnesota Living with Heart Failure (MLHF) Questionnaire [34], respectively. The EQ-5D health questionnaire is administered preoperatively and all participants complete this again at 3 months as part of the postal questionnaire.

The primary outcome is myocardial injury, assessed by measuring myocardial troponin T in serum from blood samples collected preoperatively and at 1, 6, 12, 24, and 48 hours after chest closure. The concentration of plasma propofol is measured in blood samples collected from the cardioplegia/bypass circuit immediately before aortic cross-clamping, once during cardioplegia (after blood–cardioplegia mixing), and 10 minutes after cross-clamp release.

### Sample Size

The trial is designed to test hypotheses about the superiority of the intervention.

A sample size of 96 has been chosen to enable the trial to detect a standardized difference of 0.5 between the propofol-supplemented and placebo groups, with 80% power at a significance level of 5% (2-tailed) within each surgical stratum. The target difference of 0.5 standard deviations is of moderate magnitude [35], is consistent with our experience of many of these outcomes in previous research to evaluate other cardiac surgery interventions, and is appropriate for an early phase trial. Estimation of the power of the trial assumed that the biomarkers, including the primary outcome, are measured at baseline and 5 times after the intervention and that the correlations between outcomes measured at baseline and after intervening and between postintervention outcomes measured on multiple occasions are 0.5.

### Statistical Analysis

Analyses will be based on the intention-to-treat principle, and will use data from all patients randomized (ie, the analyses will use the complete dataset). Continuous outcomes will be analyzed by regression modeling, transforming data logarithmically if required and adjusting for baseline values where available, and using mixed models for repeated measures. Mixed models allow all patients with data to be included in the analysis; that is, partial missing data (assumed missing at random) is permitted. Prerandomization and subsequent values will be modeled jointly, in preference to the prerandomization value being modeled as a covariate, to avoid the need either to exclude cases with missing preoperative measures or to impute missing preoperative values. Interactions between treatment and time will be examined and, if significant at the 5% level, results will be reported separately for each postoperative time point; otherwise, an overall treatment effect will be reported. Findings will be reported as effect sizes with 95% confidence intervals. Time in ICU/HDU will be analyzed as time-to-event data using Cox regression modeling.

The trial is not powered to detect differences in clinical outcomes and their frequencies will be tabulated descriptively in accordance with guidelines for reporting randomized controlled trials (RCTs) [36].

We do not have a prior expectation that the effect of propofol supplementation will differ by operation, but we will test for this possibility by fitting a treatment by surgery type interaction. If the interaction is statistically significant, surgery-specific effects will be reported along with the results of the interaction test. If, as anticipated, the interaction is not statistically significant at the 10% level, the overall treatment effect will be reported. Similarly, we will test the interaction of propofol supplementation with diabetic status and effects specific to diabetic status will be estimated if this interaction reaches 10% statistical significance.

The primary analysis will take place when follow-up is complete for all recruited patients. No interim analysis is planned.

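### A 5% treatment-by-time test decides whether the primary troponin T result is one overall effect or five time-point effects, raising its false-positive rate to about 8.5% under the plan's own correlations

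*Protocol article*

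**What the plan says.** The Primary Outcome section of the protocol article defines myocardial injury by serum troponin T, "collected preoperatively and at 1, 6, 12, 24, and 48 hours after chest closure". That gives one baseline and five postoperative values. No single postoperative time is singled out.

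The Statistical Analysis section plans a mixed model with the preoperative value modelled jointly with the later ones. A treatment-by-time interaction is then tested and, "if significant at the 5% level, results will be reported separately for each postoperative time point; otherwise, an overall treatment effect will be reported". The rule covers all repeated continuous outcomes, including the primary one. The word *otherwise* makes the two forms of result alternatives. Findings are to be given as effect sizes with 95% confidence intervals, and the article states no adjustment for the five time-point results.

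The Sample Size section presents a superiority trial: "A sample size of 96 has been chosen to enable the trial to detect a standardized difference of 0.5" between the arms, "with 80% power at a significance level of 5% (2-tailed) within each surgical stratum". Power was worked out on the basis that the biomarkers "are measured at baseline and 5 times after the intervention", with all correlations equal to 0.5.

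**The concern.** In a trial that declares two-sided 5% superiority testing, the primary contrast should be fixed before the data are seen. Here the same data first decide which contrast counts and then test it. Two things follow.

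- **Error rate.** A false-positive interaction test opens a branch with five further chances of a significant result, on top of the 5% already available through the overall effect.
- **Link to the sample size.** The overall effect is what the stated power appears to rest on, yet the rule omits it whenever the interaction is significant. The trial could then finish without reporting the quantity it was sized for, and with no stated way to read five results that disagree.

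The article makes a larger trial conditional on this one's result, so a clear primary answer matters.

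**Working it through.** **Inputs.** From the Sample Size section: total 96; difference 0.5 SD; 80% power; two-sided 5%; power required within each surgical stratum; one baseline and five later measures; all correlations 0.5. From the abstract: the calculation was made "assuming equal numbers in each surgical stratum", so 48 per stratum. From Randomization: "Each participant is randomly assigned in a 1:1 ratio within CABG or AVR surgery stratum", so 24 per arm per stratum.

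**Step 1: which contrast fits the stated power.** In units of the outcome SD, the variance factors are:

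- mean of five values, baseline-adjusted: (1 + 4×0.5)/5 − 0.5² = 0.60 − 0.25 = 0.35
- mean of five values, unadjusted: 0.60; as a change score: 0.60 + 1 − 2×0.5 = 0.60
- single time, baseline-adjusted: 1 − 0.5² = 0.75

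Power is approximately Φ(0.5/√(2×factor/n) − 1.96), with n per arm.

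| Contrast | n per arm for 80% | Total for two strata | Power at 24 per arm |
|---|---|---|---|
| Mean of five, adjusted | 22 (23 by t) | 88 (92 by t) | 83.3% (81.7% by t) |
| Mean of five, unadjusted or change score | 38 | 152 | 60.9% (59.0% by t) |
| Single time, adjusted | 48 | 192 | 51.6% (49.9% by t) |

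For the first row, √(2×0.35/24) = 0.171 and 0.5/0.171 = 2.93, so power is Φ(0.97) = 83%. For the last row, √(2×0.75/24) = 0.25 and 0.5/0.25 = 2.00, so power is Φ(0.04) = 52%. Of the contrasts tried, only the baseline-adjusted time average is close to 80% within a stratum.

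**Step 2: false-positive rate of the rule.** After baseline adjustment, the correlation between postoperative values is (0.5 − 0.25)/0.75 = 1/3. Suppose there is no treatment effect at any time, and call the result positive if the overall effect is significant (interaction not significant) or if any of the five times is significant at 5% (interaction significant). With this covariance the interaction statistic and the time average are independent in large samples, so:

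- no interaction found, overall effect significant: 0.95 × 0.05 = 0.0475
- interaction found, at least one time significant: 0.05 × 0.75 = 0.0375, where 0.75 comes from simulation
- sum: 0.085

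Simulation agrees: 8.5% in large samples, 8.2% at 24 per arm and 8.4% at 48 per arm. Testing each time at 1% after the gate still leaves 6.2%.

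**Step 3: sensitivity.** The residual correlation is an assumption.

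| Residual correlation | At least one time significant once the gate opens | Error of the rule |
|---|---|---|
| 1/3 (implied by the article) | 75% | 8.5% |
| 0.5 | 58% | 7.6% |
| 0.7 | 38% | 6.7% |
| 0.9 | 19% | 5.7% |

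**Step 4: how often the overall effect is dropped.** With a constant 0.5 SD effect it is dropped in 5% of trials. With an assumed profile of 0.2, 0.5, 0.8, 0.6, 0.4 SD (mean 0.5), it is dropped in about 38% at 24 per arm and 70% at 48 per arm.

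**The case against.** **The rule does not lose power.** A reader might infer from 52% against 83% that the trial becomes less likely to detect an effect present at some times only. That does not follow, because the two figures refer to different alternatives. With 0.5 SD at one time only, the average effect is 0.5/5 = 0.1 SD. The fixed average then has 9% power at 24 per arm and 13% at 48, while the rule, counting any significant time, has 40% and 71%. With a constant effect, the rule's power is practically that of the average (84% and 98.6%). This objection stands. The fault is the unfixed contrast and its error rate, not lost power.

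**An effect confined to some times need not be expected.** A marker that rises and falls in both arms shows a time effect, not an interaction. The article allows log transformation, and a constant proportional reduction would then give no interaction. It nowhere predicts an effect limited to certain times. This stands too.

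**The other interaction tests.** A reader might add the surgery-type and diabetes tests, both at 10%, and quote a larger combined error. Those are separate rules. For diabetes the article says only that specific effects would be estimated, not that they replace the main result, and a combined figure would need a diabetic proportion it does not give. They are left out here.

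**The success rule is supplied by this review.** The article does not say that one significant time point would count as success, its objectives speak of estimating mean differences, and it calls the trial early phase. A separate analysis plan may also hold an adjustment. This limits the size of the point. It does not remove it: superiority testing at 5% is declared, and the faulty rule is stated in print rather than left open.

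**The time average is inferred.** The article never names the contrast behind its power figure. A single-time adjusted analysis pooled over both strata (48 per arm) also gives about 80%, but the article puts the power within each stratum.

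**Conclusion.** The point holds and should be fixed; it is moderate in size. The protocol lets a preliminary test choose the primary contrast. Under the article's own correlations this raises the false-positive rate from 5% to about 8.5%, and by less if postoperative values are more strongly correlated. That figure rests on counting any significant time point as a positive result, since the article gives no other criterion, and on no adjustment being applied. It is well short of the roughly 20% that five unconditional tests would give, because the five-test branch is entered in only 5% of null trials.

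Separately, the rule can omit the one contrast that fits the stated power within each stratum.

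**What to change.** Name the treatment difference in troponin T averaged over the five postoperative times, adjusted for baseline through the joint model, as the primary result. Estimate it, test it at 5% and report it whatever the interaction test shows. Always present the five time-specific estimates and the interaction p-value as secondary. If any single time is to support a claim, apply Holm or Hochberg across the five.

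This restores a 5% error rate, with 82–83% power per stratum for a constant 0.5 SD effect. Correcting the five tests while keeping the gate would not be enough, as the 6.2% above shows.

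The cost is a change of analysis wording, with no further patients or samples. The downside is that time-specific findings become secondary, and an effect confined to one or two times would probably be missed by the primary test. The time-specific results must therefore be shown in every case.

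### Objectives and power are set within each surgical stratum, but the reporting rule defaults to the pooled effect and does not guarantee the CABG and AVR estimates

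*Protocol article*

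**What the plan says.** Three places set the target within each operation.

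- The Introduction ends with two specific objectives. The first is "To estimate mean differences in biomarkers of cardiac injury and metabolism between groups of participants having isolated CABG with CPB", with warm blood cardioplegia; the second is its counterpart for AVR, with cold blood cardioplegia. No pooled objective is listed.
- The Abstract (Methods) says: "The trial is designed to test hypotheses about the superiority of the intervention within each surgical stratum".
- Sample Size says: "A sample size of 96 has been chosen to enable the trial to detect a standardized difference of 0.5", and continues, "with 80% power at a significance level of 5% (2-tailed) within each surgical stratum".

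Statistical Analysis sets a different rule. The authors have no prior expectation that the effect differs by operation. They will fit a treatment-by-surgery interaction and report surgery-specific effects if it is significant. On the other branch: "If, as anticipated, the interaction is not statistically significant at the 10% level, the overall treatment effect will be reported". Nothing in the article provides for stratum estimates on that branch.

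**The concern.** The trial is described and sized to answer two questions, one per operation, but the reporting rule lets a preliminary test decide whether those answers are called for. On the branch the authors anticipate, the article commits only to an average over the two operations.

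The strata are not interchangeable by design: they differ in cardioplegia temperature and in how the supplement is delivered. A non-significant interaction in 96 patients does not show that the effects are equal, so a benefit confined to one operation could be presented as an overall benefit. When the interaction test does pass, the stratum contrast has been selected for being large and will tend to be exaggerated. The result matters beyond this trial, because a larger trial is planned if the hypothesis is confirmed and the authors expect the findings to apply to almost all standard CABG or AVR patients.

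**Working it through.** **Inputs.** The total is 96, the target 0.5 SD, the test two-sided at 5%, with one baseline and five later measurements and all correlations 0.5 (Sample Size). Strata are equal: "assuming equal numbers in each surgical stratum" (Abstract, Methods). Allocation is 1:1 within stratum (Randomization). This gives 96/2 = 48 per stratum and 24 per arm per stratum. The interaction level is 10% (Statistical Analysis). The article states no dropout allowance, so none is used.

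**1. Reproduce the plan's power.** The variance factor for the mean of five later values, adjusted for baseline, is (1 + 4×0.5)/5 − 0.5² = 0.60 − 0.25 = 0.35.

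- One stratum: SE = √(2×0.35/24) = 0.171 SD. Power for 0.5 SD = Φ(0.5/0.1708 − 1.960) = Φ(0.968) = 83.3%, or 81.8% with the t distribution. The stated 80% is reproduced as a within-stratum figure.
- Pooled, 48 per arm: SE = √(2×0.35/48) = 0.121 SD. Power = Φ(0.5/0.1208 − 1.960) = Φ(2.180) = 98.5%, or 98.4% with t. The stated 80% does not describe this analysis.

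**2. How often the rule calls for stratum effects.** The SE of the difference between strata is √2 × 0.1708 = 0.242 SD.

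| True effects (SD) | Interaction p < 0.10 | Not triggered |
|---|---|---|
| 0.5 and 0.5 | 10% | 90% |
| 0.5 and 0.25 | 27.5% | 72.5% |
| 0.5 and 0 | Φ(0.5/0.2415 − 1.645) = Φ(0.425) = 66.5% | 33.5% |

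The interaction test reaches 80% power only for a between-stratum difference of (1.645 + 0.842) × 0.2415 = 0.60 SD, which is larger than the trial's own target effect.

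**3. Significant pooled effect when one operation has none.** With true effects of 0.5 and 0, the pooled effect is 0.25 SD and its power is Φ(0.25/0.1208 − 1.960) = Φ(0.110) = 54.4%. With equal strata the average and the difference are independent, so the interaction is non-significant and the pooled effect significant in 0.335 × 0.544 = 18.2% of all trials. A simulation of 2,000,000 draws gave 18.3%.

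**4. Size of a selected contrast.** If the true effects are equal, the 10% of trials that pass the test show a mean absolute stratum difference of 0.2415 × 2φ(1.645)/0.10 = 0.2415 × 2 × 0.1031/0.10 = 0.50 SD. The truth is 0. The signed mean is also 0, because the error falls equally in either direction.

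**5. False positives.** With no effect anywhere, two separate 5% stratum tests give 1 − 0.95² = 9.75%. The two-stage rule gives 9.4% by simulation.

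**The case against.** The best defence has four parts.

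- **The rule does not forbid stratum estimates.** This stands. The section says what will be reported on each branch; it does not say that stratum effects are barred when the interaction is non-significant. A reader might infer that the objectives will be withheld, but the text does not go that far. The 90% and 34% are rates at which the rule fails to call for stratum effects, and they become rates of non-reporting only on the strictest reading. The full protocol or a statistical analysis plan may specify stratum tables. The conflict between the stated rule and the stated objectives would remain in this document.
- **The overall effect is a legitimate quantity.** This also stands. Under stratified randomization it is a valid average, and testing an interaction before pooling can suit a trial whose objective is pooled. Here the objectives and power are not. The 18% refers to a significant average; that it would be claimed separately for each operation is an inference. It also belongs to one chosen scenario, while the authors expect no difference.
- **The preliminary test does not inflate error relative to the stated design.** A reader might infer from the 9.4% that the gate raises a 5% error rate. That comparison assumes a single pooled test, which is not the design in the Abstract or Sample Size. Against two 5% stratum tests (9.75%) the gate is slightly lower. The multiplicity comes from having two strata.
- **The trial is early phase with a biomarker outcome.** This is true, and randomization, data collection and the number of patients are unaffected.

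**Conclusion.** The concern holds as an inconsistency between the stated objectives and power, which are per stratum, and the reporting rule, whose anticipated result is pooled. Followed as written, the rule can leave both listed objectives unanswered; it does not make that certain.

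The rule fails to call for stratum effects in 90% of trials when both effects are 0.5 SD and in about 34% when the effects are 0.5 and 0. In the latter case about 18% of all trials give a significant pooled result although one operation has no effect. These figures assume 48 per stratum, no missing data, all correlations 0.5 and normal approximations. They also take the 10% level, which is attached in the text to the non-significant branch, as applying to both branches.

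The sample size itself is sound for the stratum objectives. The documents do not settle whether the stratum effects or the pooled effect should be confirmatory, so that is for the trial team to decide and state.

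**What to change.** 1. Report the CABG and AVR effects with 95% confidence intervals from the interaction model, whatever the interaction p-value, and treat that p-value as descriptive.
2. State in advance which contrast is confirmatory, and align the Abstract, the objectives, Sample Size and Statistical Analysis with it. Either choice is coherent:
   - **Both stratum effects.** Power is about 82–83% each for 0.5 SD at 48 per stratum, so no more patients are needed for two tests at 5%. The plan should say how the two tests are handled, since together they carry about a 9.8% chance of at least one false positive. Any stricter level would lower the 82–83%.
   - **The pooled, surgery-adjusted effect.** Power is about 98% for 0.5 SD, so the 80% statement must be restated and a pooled objective added. The stratum effects are then reported as supporting estimates.

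The cost is wording in four places and one extra row of estimates from a model the plan already fits. No new data are needed.
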